#### Cost evaluation

Costs of the implementation strategies in relation to the number of correctly referred patients.

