### Interventions

#### Implementation strategies in both groups

In both the control group and the intervention group, clinicians will receive the FHCC guideline.

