#### Website

The website consists of the following items:

1. A summary of evidence-based and relevant information about familial CRC risk (lifetime risk of developing CRC). Natural frequencies with the same denominator and visual displays will be used. Absolute risks will be presented, as well as in comparison to the population risk. The outcomes are offered in both positive and negative frames (*e.g*., the risk of developing CRC as well as the chance of not developing CRC). The focus is on familial CRC risk and the different follow-up policies. The information is presented in two different formats, one for patients and one for clinicians.

2. A risk assessment tool to calculate patients' familial CRC risk. Patients fill in medical information about themselves and their relatives with regard to CRC and other cancers. Clinicians can use the tool as well. The calculated familial CRC risk is given in the same format as the rest of the website. Advice for follow-up is offered based on this risk, as well as a reminder to use the corresponding decision aid, if applicable.

3. Decision aids, aimed at facilitating decisions involving the uptake of the indicated follow-up policy (one for surveillance and one for genetic counselling). Tools supporting patients in making informed choices about their healthcare, such as decision aids, have been shown to improve knowledge, clarify preferences, and reduce uncertainty around decision making, with high levels of acceptability among consumers[20,21]. The decision aids used in this trial provide balanced information on different options, *i.e*., to be referred for surveillance/genetic counselling or not. The following items are addressed: background information, benefits and harms, and the potential impact on the patient and their relatives. Worksheets are provided for patients to list and rate the importance of the benefits and harms for themselves.

The website is available exclusively to patients and clinicians in the intervention group. A login name and password will be provided upon inclusion. Patients can use the website independently before or after regular follow-up visits, and are encouraged to discuss the results with their clinician. They are instructed to keep the decision aid within their family, and not share it for reasons of research integrity. To minimize contamination bias, after the trial all patients in the control group will be asked if they were exposed to the website.

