#### Effect evaluation

Before introducing the implementation strategies, a baseline assessment of risk calculation, interpretation, and communication will be performed. Both the baseline assessment and the evaluation of the implementation strategies will be performed retrospectively in the same manner. Baseline characteristics will be collected in the manner described above. The measuring instruments will be developed by identifying all relevant variables and translating these into questionnaires. When possible, existing validated questionnaires will be used.

The family history as reported by the patient in the questionnaire will be used to calculate a formal familial CRC risk and determine the indicated follow-up policy. This will be compared to the family history taken by the clinician, along with the risk calculation and interpretation performed by the clinician. These data will be extracted from the patients' medical records. The medical records will also be used to determine the number of patients with whom the familial CRC risk and corresponding follow-up policy has been communicated. To determine the number of referred patients who actually visit a familial cancer clinic, these clinics will be asked to report whether these patients have visited. The uptake of surveillance by colonoscopy by first-degree relatives will be determined by asking the patients whether their relatives are actually screened. Medical records and results from the decision aids on the website will be used to determine whether patients at an increased risk who were not referred for surveillance or genetic counselling were not referred because they had chosen not to be referred or because it was not discussed.

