### Data analysis

#### Effect evaluation

To analyze the effectiveness of both implementation strategies, descriptive statistics and multilevel analysis will be used. Patient, clinician, and hospital characteristics will be included in the multilevel analysis, allowing for correction of the effectiveness for probable differences in case mix between the different hospitals. The statistical analyses will be performed using SPSS version 16.0 for Windows.

The percentage of correctly referred patients is defined as follows:

1. The percentage of patients at an average familial CRC risk who are not referred for surveillance or genetic counselling.

2. The percentage of patients at a moderate familial CRC risk who want to be referred and are referred for surveillance.

3. The percentage of patients at a moderate familial CRC risk who do not want to be referred and are not referred for surveillance.

4. The percentage of patients at a high familial CRC risk who want to be referred and are referred for genetic counselling.

5. The percentage of patients at a high familial CRC risk who do not want to be referred and are not referred for genetic counselling but are referred for surveillance if they opt for it.

6. The percentage of patients at a high familial CRC risk who do not want to be referred and are not referred for genetic counselling or surveillance.

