### Strengths and weaknesses

To our knowledge, this is the first study of an implementation strategy designed to improve the recognition of patients' familial CRC risk by addressing both patients and their clinicians (surgeons and gastroenterologists). If the intensive implementation strategy is successful, the elements (the website and the risk communication tool) can be released for general use by patients and clinicians. They may also serve as an example for other hereditary and non-hereditary diseases. Our study will add knowledge to the effectiveness of patient decision aids and the best way of supplying patients and clinicians with information on disease risks.

Some limitations need to be addressed. Family history as reported by the clinician will be compared to the family history reported by the patient in a self-administered questionnaire. Previous research has shown that the accuracy of family history of CRC in first-degree relatives reported by patients is approximately 90%[22]. The optimal way of ensuring that the family history reported by the patient is accurate is by reviewing medical records of the affected relatives. Since written permission from relatives is needed to do so, this is not feasible and will therefore not be done in this study.

In our evaluation, only patients will be included; their relatives are not. Patients will be asked whether their relatives are screened, but the relatives will not be contacted to assess whether they actually received the results from the risk assessment and the matching advice.

Measurements may be contaminated in case others are provided with the login code for the website.

Collecting data from medical records does not monitor everything that is discussed between the clinician and the patient. This may lead to underestimation of the risk interpretation and communication. Videotaping the consultations would shed light on the content and quality of the risk communication, but would also influence the intervention by reminding the clinician of the intervention. In this study, regular clinical practice will be left undisturbed as much as possible.

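### Refusal of referral is ascertained partly from decision aids that only the intervention arm has, so the correctly-referred percentage and the cost per correctly referred patient could favour the intervention

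*Protocol article*

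**What the plan says.** Four parts of the protocol article bear on this point.

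- **Source of the classification** (Data collection, Effect evaluation). "Medical records and results from the decision aids on the website will be used to determine whether patients at an increased risk" and had no referral "were not referred because they had chosen not to be referred or because it was not discussed". Two sources and two categories are named.
- **Who has the second source** (Interventions, Website). The decision aids are part of the website, and "The website is available exclusively to patients and clinicians in the intervention group". What both arms share is the guideline: "In both the control group and the intervention group, clinicians will receive the FHCC guideline".
- **What the classification decides** (Data analysis, Effect evaluation). Among the six components of correct referral, item 3 is "The percentage of patients at a moderate familial CRC risk who do not want to be referred and are not referred for surveillance". Item 6 covers high-risk patients "who do not want to be referred and are not referred for genetic counselling or surveillance". Item 5 covers high-risk patients who decline genetic counselling but may opt for surveillance.
- **Where the count is used again** (Outcome measures, Cost evaluation). The outcome is "Costs of the implementation strategies in relation to the number of correctly referred patients".

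On the source common to both arms, Strengths and weaknesses concedes: "Collecting data from medical records does not monitor everything that is discussed between the clinician and the patient". It draws the consequence only for risk interpretation and communication. It does not mention that the sources for the reason for non-referral differ between arms.

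**The concern.** Part of an outcome is measured with an additional instrument in one arm, and that instrument is itself a component of the intervention. For a non-referred moderate- or high-risk patient, correct or incorrect turns on whether a refusal can be found. In the intervention arm there are two places to find it; in the control arm only one is named. A refusal absent from the record can be recovered in the first arm and not in the second.

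There is a related problem. Patients may use the website on their own and are only encouraged to discuss the result with the clinician. If a refusal seen only on the website is accepted, a patient with whom the clinician never raised referral could be scored as correctly referred. That would hide the omission the strategy is meant to correct.

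At stake is whether a higher correctly-referred percentage, or a favourable cost per correctly referred patient, could be attributed to the strategy rather than to better capture of refusals.

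**Working it through.** **The plan's own figure.** The document gives no number for this classification. The nearest is the Power calculation: a 20-point difference, two-sided alpha 0.05, power 0.80, 186 patients. The base rate is not stated. Assuming 30% versus 50% (50% versus 70% gives the same), the pooled-variance formula gives 93 per arm, and 2 × 93 = 186. The design effect is 1 + (5 − 1) × 0.15 = 1.6, and 186 × 1.6 = 297.6, about the stated 300. The figure reproduces, but it concerns uptake of colonoscopy and referral for genetic counselling, not correct referral.

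**How one patient is scored.** Take an increased-risk patient who declined, was not referred, and whose record is silent.

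| | Control | Intervention |
|---|---|---|
| Named sources | record | record and decision aid |
| Refusal found? | no | yes, if the aid shows it |
| Category, if silence means not discussed | not discussed | declined |
| Correctly referred? | no | yes |

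**Formula with no true difference between arms.** Among increased-risk patients let

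- r = share correctly referred because the referral was made;
- d = share who declined and were not referred;
- s = chance that the record shows the refusal, equal in both arms;
- a = chance that the aid shows a refusal the record misses.

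Control share = r + d·s. Intervention share = r + d·[1 − (1 − s)(1 − a)]. The false difference is d·(1 − s)·a, which is never negative under the rule that silence means not discussed.

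**Numbers.** All values of r, d, s and a are assumptions; the document gives none.

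- Example: r = 30%, d = 20%, s = 0.5, a = 0.5. Control 0.30 + 0.20 × 0.5 = 40%. Intervention 0.30 + 0.20 × 0.75 = 45%. Difference 5 points.
- Low: 0.10 × 0.2 × 0.25 = 0.005, or 0.5 points.
- High: 0.30 × 0.7 × 0.8 = 0.168, or about 17 points.

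**Dilution in the cost count.** That count also includes the average-risk patients of item 1, who are unaffected. The Background puts familial and hereditary cancers at about 15 to 20% of CRC. If that approximates the increased-risk share of the sample (an assumption), the 5-point example becomes 5 × 0.15 = 0.75 to 5 × 0.20 = 1.0 points of all patients.

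**Does the baseline measurement help?** Data collection says that baseline and evaluation are done in the same way. For this item they cannot be, because the website belongs to the strategy introduced after baseline. Comparison with baseline would not remove the difference in sources.

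**Same sources in both arms.** Setting a = 0 makes both shares r + d·s, and the false difference is zero.

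**The case against.** Several counter-arguments have force.

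- **The powered comparison is different.** A reader might set the possible bias against the 20-point target and conclude that it could supply much of the planned effect. The document does not support that. The target is for uptake and referral. Uptake is measured from familial cancer clinics' reports of visits and from patients' answers about their relatives, without decision-aid input. None of the four listed effect outcomes is named as correct referral. This stands.
- **Reach is limited.** Only non-referred moderate- and high-risk patients under items 3, 5 and 6 are exposed. If the denominators are whole risk groups, which the text does not fix, items 2 and 4 are untouched. This stands.
- **The direction rests on an unstated rule.** The article gives no rule for silent or conflicting sources. If an aid showed a wish for referral against a recorded refusal, that patient could move the other way. It is also not stated that a website-only refusal counts, or that the aid, described as worksheets for weighing benefits and harms, logs a final decision. So the analysis could show a false benefit; it is too strong to say that it would. The two-way split does make the silent-means-not-discussed reading the natural one.
- **Some of the difference may be real.** The aids are meant to support an informed choice, and the strategy may prompt discussion and recorded refusals. True, but the planned measurement cannot separate that from better capture.
- **The article is condensed.** Questionnaires are to be developed, and a preference item for both arms cannot be excluded. None is named as a source for this classification, however, and even with one, decision-aid data in one arm only would leave ascertainment unequal. The point concerns a stated rule, not a missing detail.

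**Conclusion.** The concern holds as a matter of unequal ascertainment. The article states that the reason for non-referral is read from records and decision aids, restricts the aids to the intervention arm, and makes that reason decide part of the correctly-referred definition and the cost outcome. Nothing elsewhere in the article repairs this.

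The bias could favour the intervention with identical clinician behaviour, provided that a silent record is treated as not discussed and that the aid reveals refusals which records miss. Its size is not computable from the document. The 0.5 to 17 points among increased-risk patients is an illustration over assumed inputs, and the effect on the all-patient cost count is smaller. The documents do not support the stronger readings: that the powered uptake and referral comparison is directly biased, that a false benefit is certain, or that any difference seen would be wholly spurious.

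**What to change.** 1. Classify the wish to be referred from the same sources in both arms: the medical record plus one identical item in the patient questionnaire, asking whether referral was offered and whether the patient wanted it. State how silent and conflicting sources are handled, and apply that rule equally in both arms.
2. Use decision-aid output only in the process evaluation.
3. Also report, for all moderate- and high-risk patients, whether the indicated referral was made (yes or no), regardless of preference. This result does not depend on ascertaining preference. It counts informed refusals as not referred, so it belongs beside the preference-based result and does not replace it.

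The cost is one or two items in a questionnaire that patients already receive, and a revised classification rule. Recall error is possible, but the instrument then has the same form in both arms.

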#### Process evaluation

In the process evaluation, data are collected on actual exposure of patients and clinicians to the different elements of the implementation strategies, as well as their experience with these elements:

1. Website: The website automatically records the following data when it is used: who used which elements; how often did users visit the different elements of the website; and how long did it take to use the different elements. By using questionnaires, users' experiences with the website will be ascertained.

2. Education: Attendance at the meetings will be determined by keeping an attendance list. The duration of the meetings will be recorded. In addition, clinicians' experience with the meetings will be ascertained by using a questionnaire.

3. Risk communication tool: Patients and clinicians will be asked whether the tool was used. Their experience with the tool will be measured using questionnaires focussing on the perceived usefulness and usability of the tool.

#### Cost evaluation

Costs accompanied with the development and implementation of the website and risk communication tool will be accounted for, as well as the costs for dissemination of the guideline. Clinicians will provide time estimates to use the different elements. Costs will be correlated to the number of correctly referred patients.

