#### Intensive implementation strategy in the intervention group

The intensive implementation strategy is summarized in Figure 1 and consists of the following implementation tools: a website for patients and clinicians; education for clinicians; and a risk communication tool for clinicians.

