#### Cost evaluation

The costs of implementation related resource use will be calculated on a per patient basis. The costs of the use of each element per correctly referred patient will be calculated. The costs of the intensive implementation strategy will be compared to the costs of dissemination of the guideline only.

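### The list of costs omits the set-up of the educational meetings, one of three tools in the intensive strategy, and the only ratio stated is an average that does not price an additional correct referral

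*Protocol article*

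**What the plan says.** The section on the intensive strategy names three tools: "a website for patients and clinicians; education for clinicians; and a risk communication tool for clinicians". Both groups receive the guideline; only the intervention group has the meetings.

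Data collection, Cost evaluation, lists what is costed: "Costs accompanied with the development and implementation of the website and risk communication tool will be accounted for". The same sentence includes the cost of distributing the guideline. The section then turns to time: "Clinicians will provide time estimates to use the different elements".

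Data collection, Process evaluation, treats education as one of the elements. An attendance list is kept, and "The duration of the meetings will be recorded".

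The cost outcome is "Costs of the implementation strategies in relation to the number of correctly referred patients". Data analysis, Cost evaluation, gives the calculation, "The costs of the use of each element per correctly referred patient will be calculated", and a comparison between strategies: "The costs of the intensive implementation strategy will be compared to the costs of dissemination of the guideline only".

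Data analysis, Effect evaluation, defines correct referral in six categories. The first is average-risk patients who are referred for neither surveillance nor genetic counselling.

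**The concern.** There are two separate problems.

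**Cost list.** The list does not match the article's own definition of the intervention. The website and the communication tool are costed for development and implementation. The meetings, which occur in one arm only, get no such line. Leaving out an item used only in the intervention arm can move the comparison in one direction only: the intensive strategy looks cheaper than it is.

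**Ratio.** Cost per correctly referred patient divides by everyone handled correctly, including those who would have been handled correctly with the guideline alone. The article's abstract says the results should help identify the most effective method and its costs. A hospital deciding whether to move from dissemination to the intensive strategy needs the extra cost per extra correct referral, and the article does not state that it will be calculated.

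**Working it through.** The article gives no cost figure, so there is none to reproduce.

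**1. Tools against cost lines**

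| Tool | Set-up and delivery cost named? | Users' time |
|---|---|---|
| Website | Yes | Clinicians' time estimates |
| Risk communication tool | Yes | Clinicians' time estimates |
| Educational meetings | No | Possibly the time estimates; attendance and duration are recorded, but for the process evaluation |
| Guideline (both arms) | Yes, dissemination | not relevant here |

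Whether the time estimates reach the meetings depends on what *elements* means. Data collection, Process evaluation, counts education as one. The Discussion, Strengths and weaknesses, glosses the elements as the website and the risk communication tool only, the same pair as in the cost list. On either reading, trainers, preparation and organisation of the meetings are not covered.

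**2. Effect of the omission**

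Let *e* be the share of the true intensive-strategy cost that goes uncounted. The counted cost is (1 − *e*) times the true cost. The article does not give *e*; assumed values are:

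- *e* = 10%: 90% of the true cost is counted
- *e* = 25%: 75%
- *e* = 50%: 50%

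**3. Average against incremental ratio**

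Let C1 and C0 be the cost per patient under the intensive and common strategies, and p1 and p0 the proportions correctly referred.

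- Average = C1 / p1
- Incremental = (C1 − C0) / (p1 − p0)

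Assume C1 = 100 and a gain of 20 percentage points. The Power calculation states 20% for uptake and referral in moderate- and high-risk patients. It is borrowed here for illustration only, and p0 is assumed.

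| p0 → p1 | Average | Incremental, C0 = 10 | C0 = 50 | C0 = 90 |
|---|---|---|---|---|
| 0.3 → 0.5 | 100/0.5 = 200 | 90/0.2 = 450 | 50/0.2 = 250 | 10/0.2 = 50 |
| 0.5 → 0.7 | 100/0.7 = 142.9 | 450 | 250 | 50 |
| 0.7 → 0.9 | 100/0.9 = 111.1 | 450 | 250 | 50 |

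Rearranging the two formulas, the incremental ratio exceeds the average when C0/C1 < p0/p1. For the three rows this means C0/C1 below 0.3/0.5 = 0.60, 0.5/0.7 = 0.71 and 0.7/0.9 = 0.78. Dissemination alone should be cheap relative to a strategy that adds a website, a tool and meetings, so the average will probably be the lower figure, but this is not guaranteed. The average also changes with p0 when the gain and the costs are the same, which shows that it does not measure what the extra spending buys.

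**The case against.** The best reply is that, read as a whole, the article does cost education. The time estimates and the analysis refer to elements, the process evaluation lists education among them with attendance and duration, and the cost comparison concerns the intensive strategy, which by definition includes education. This stands in part. A reader might infer that the meetings are wholly uncosted, and the text does not establish that: clinicians' time may well be included. Trainer, preparation and organisation costs still have no line, while the other two tools have one.

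A second reply is that an article may leave costing detail to the full protocol, and that with costs and effects for both arms an incremental ratio can be formed anyway. That is fair for finer detail such as intervals or a split of one-off from recurring costs, which are not raised here. But the cost list that is printed does not match the intervention, and the ratio that is printed is the average one. Nor would it be right to say that the strategies are not compared: their costs are, but the cost difference is not related to the difference in effect.

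Three further inferences are tempting and unsupported:

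- **That the average ratio understates the cost of the strategy.** The choice of ratio does not change total cost.
- **That the omission can be put in hours.** No meeting length is given, and clinician time is the part most likely to be captured. Scaling to at-risk patients by the 15 to 20% in the Background is also weak: that figure is the familial and hereditary share of all colorectal cancers, while the Power calculation words its 300 patients in terms of moderate and high risk.
- **That the denominator should be confined to moderate- and high-risk patients.** The article deliberately counts average-risk patients who are not referred and names overuse as a source of unnecessary cost. Restricting the main result would discard avoided over-referral.

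**Conclusion.** The point holds in two limited parts.

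First, the cost list leaves out the trainer, preparation and organisation costs of the meetings. Applied as written, it understates the cost of the intensive strategy. The direction is clear because the meetings exist in one arm only. The size is unknown, and the 10 to 50% shares above are assumptions, not estimates.

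Second, the stated ratio does not give the cost of an additional correctly referred patient. With a cheap comparator it probably looks more favourable than the incremental ratio (142.9 against 450 in the middle row with C0 = 10). The gap depends entirely on assumed costs and proportions, and the order reverses if the common strategy costs nearly as much as the intensive one.

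Neither part touches the effect evaluation. Both bear on the cost evaluation, one of the trial's three stated evaluations, and both are cheap to put right.

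**What to change.** 1. In Data collection, Cost evaluation, name the educational meetings as a cost item: preparation, trainers, organisation, and clinician time taken as attendance multiplied by recorded duration. Count that clinician time once, not again through the time estimates.
2. Use *elements* in one sense, including education, in the sections on the intensive strategy, data collection, data analysis, and strengths and weaknesses.
3. In Data analysis, Cost evaluation, add the incremental cost per additional correctly referred patient, intensive versus common, using the definition of correct referral in Data analysis, Effect evaluation. Report the moderate- and high-risk subset as a supplementary result. The per-element averages can stay as description.

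The price is one extra cost line, one extra calculation and a somewhat higher stated cost for the intensive strategy. Attendance and duration are already recorded; trainer, preparation and organisation costs need to be noted as the meetings are held.
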